### Study steering committee

The study steering committee comprises an independent chairperson (a consultant nephrologist), a second independent consultant nephrologist, a patient advocate, the study statistician, an independent statistician, the chief investigator, the study lead research nurse and one other co-investigator.

### Data analysis

#### Prospective longitudinal cohort study

Data will be analysed to address three main questions:

1. Which of the GFR-estimating equations is the most accurate assessment of reference GFR?

2. Which GFR-estimating equation most accurately reflects change in GFR?

3. Which GFR-estimating equation, together with ACR, or ACR alone, most accurately predicts those people that have progressive loss of kidney function (CKD progression)?

In each case, data will be further analysed to assess whether observed relationships amongst African-Caribbean and South-Asian subjects differ from those observed amongst Caucasians, and whether diabetes and proteinuria are predictors.

1. Which of the GFR-estimating equations is the most accurate assessment of reference GFR?

Accuracy will be assessed by establishing the proportion of GFR estimates within 30% (P_30_) of iohexol GFR, using baseline measures. P_30_ values will be compared between GFR estimating equations using McNemar’s test for paired data. Additional analysis will consider the mean and median, interquartile range and root mean square error of the distribution of differences.

2. Which GFR-estimating equation most accurately reflects change in GFR?

Rate of change in eGFR will be established by linear regression [54] utilising all available (maximum 7) eGFR time points, and will be compared with the difference between final and baseline reference GFR values. Differences in large error rates (greater than 3 mL/min/1.73 m^2^/year, or greater than 5%/year difference in slope) will be compared using McNemar’s test. Additional analyses will consider the predictive ability of the tests to detect i) a change in iohexol GFR of greater than 25%; ii) a decline in GFR of greater than or equal to 10 mL/min/1.73 m^2^ over the three years; and iii) a change that exceeds the RCV derived for the reference GFR test in the measurement variability study described below.

3. Which GFR-estimating equation, together with ACR, or ACR alone, most accurately predicts those people that have progressive loss of kidney function (CKD progression)?

Models will be constructed to predict time to progression based on baseline eGFRs and ACR. Progression will be defined in terms of decline in reference GFR (change in iohexol GFR > 10 mL/min/1.73 m^2^) or an increase in albuminuria category, as suggested by KDIGO [38]. Progression will only be detected at one of 6 time points, hence piecewise survival models will be fitted to determine whether the prognostic value of ACR and the estimated GFRs is independent of other risk factors. We will develop a prognostic model utilising age, gender, ethnicity, body mass index, waist circumference, mean arterial blood pressure, diabetes mellitus, smoking status, and presence of vascular disease in addition to baseline ACR and the various eGFRs. Both proportional and non-proportional hazards will be considered. Bootstrap validation will be used with these prediction models.

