**Methods/design:**

Iohexol measured GFR will be the reference against which each estimating equation will be compared. The estimating equations will be based upon serum creatinine and/or cystatin C. The eGFR-C study has 5 components:

1) A prospective longitudinal cohort study of 1300 adults with stage 3 chronic kidney disease followed for 3 years with reference (measured) GFR and test (estimated GFR [eGFR] and urinary albumin-to-creatinine ratio) measurements at baseline and 3 years. Test measurements will also be undertaken every 6 months. The study population will include a representative sample of South-Asians and African-Caribbeans. People with diabetes and proteinuria (ACR ≥30 mg/mmol) will comprise 20-30% of the study cohort.

2) A sub-study of patterns of disease progression of 375 people (125 each of Caucasian, Asian and African-Caribbean origin; in each case containing subjects at high and low risk of renal progression). Additional reference GFR measurements will be undertaken after 1 and 2 years to enable a model of disease progression and error to be built.

3) A biological variability study to establish reference change values for reference and test measures.

4) A modelling study of the performance of monitoring strategies on detecting progression, utilising estimates of accuracy, patterns of disease progression and estimates of measurement error from studies 1), 2) and 3).

5) A comprehensive cost database for each diagnostic approach will be developed to enable cost-effectiveness modelling of the optimal strategy.

The performance of the estimating equations will be evaluated by assessing bias, precision and accuracy. Data will be modelled as a linear function of time utilising all available (maximum 7) time points compared with the difference between baseline and final reference values. The percentage of participants demonstrating large error with the respective estimating equations will be compared. Predictive value of GFR estimates and albumin-to-creatinine ratio will be compared amongst subjects that do or do not show progressive kidney function decline.

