### Sample size calculations

1) Prospective longitudinal cohort study

The sample size calculation for the main study focuses on the ability to detect differences in accuracy of measurement between the MDRD_creatinine_ equation and the CKD-EPI_cystatin C_ equation. We will also make secondary comparisons with the other equations**.** The measure of accuracy we will use is the P_30_. Sample size is based on a simulation study to estimate differences in P_30_ and estimates of rate of change which are not amenable to algebraic solution. Our simulation modelled the full structure of the study including random variability, and computed statistical power through noting the percentage of simulations yielding statistically significant results (P < 0.05) for analysis of each outcome. Power estimates are based on 1000 simulations.

With 1000 evaluable subjects our simulations showed the study to have 87% power at the 5% significance level to detect a difference of 5% in P_30_, between 81% and 86%, which is of a magnitude considered clinically important and likely to occur with the expected scale of differences in imprecision between the equations [27]. We thus aim to recruit 1300 people, which allowing for 15-20% drop-out will deliver over 90% power. The proposed sample size in the ethnicity subgroups will allow P_30_ estimates to be reported with 95% confidence intervals of 10 percentage points wide.

Rates of change in estimated and measured GFR will be obtained by linear regression. Padala et al. proposed two cut-points for estimating accuracy of rates of change: greater than 3 mL/min/1.73 m^2^/year error and greater than 5% error [54]. The study will have over 90% power and over 80% power at the 5% significance level to detect differences in these two outcomes respectively, for differences of a magnitude corresponding with P_30_ measures of 81% and 86%.

2) Sub-study of patterns of disease progression

A sample size of 375 was chosen based on practical considerations to allow investigation of twelve covariates of interest (gender, age, diabetes, duration of diabetes, ethnicity, albuminuria, baseline GFR, blood pressure, body mass index, waist circumference, smoking status and presence of vascular disease) in addition to variables for time, drug effects and random effects. Another consideration was to include a reasonable number of subjects in each of the ethnic groups and high and low risk subgroups to estimate disease progression.

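### Question 2 tests slope error only as large error yes/no; a paired full-scale comparison between equations should be added beside McNemar's test

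*Protocol article*

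**What the plan says.** Under Data analysis, Prospective longitudinal cohort study, question 2, each participant's eGFR slope comes from a linear regression on up to seven time points and is set against the change in iohexol GFR from baseline to the end. The test follows: "Differences in large error rates (greater than 3 mL/min/1.73 m^2^/year, or greater than 5%/year difference in slope) will be compared using McNemar’s test". The additional analyses for this question take three yes/no targets: an iohexol change above 25%, a decline of at least 10 mL/min/1.73 m², and a change beyond the reference change value.

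Under Sample size calculations, the cuts are attributed to a published study: "two cut-points for estimating accuracy of rates of change: greater than 3 mL/min/1.73 m^2^/year error and greater than 5% error". On power the article says: "The study will have over 90% power and over 80% power at the 5% significance level to detect differences in these two outcomes respectively". The effect assumed there is the one taken to match P30 values of 81% and 86%. The abstract agrees: "The percentage of participants demonstrating large error with the respective estimating equations will be compared".

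Question 1 also uses McNemar's test, on P30, but adds the mean, median, interquartile range and root mean square error of the differences. Question 2 has no matching sentence.

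**The concern.** The quantity of interest is continuous and paired: eGFR slope minus annualised iohexol change, for each equation in the same person. Once it is cut, errors of 3.1 and 10 mL/min/1.73 m²/year count the same and an error of 2.9 counts as none. Noise in the iohexol difference is shared by the equations being compared and moves people across the cut for reasons unrelated to either equation.

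The objectives section makes superiority in detecting change in GFR an explicit aim and says that no study has addressed it. If McNemar's test on the cuts is the only formal comparison, a real difference in how well two equations track GFR has a greater chance of being missed than the collected data require.

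**Working it through.** **Inputs from the article.** P30 81% v 86%; 1000 evaluable; 87% power for P30; over 90% and over 80% power for the two slope outcomes; seven visits over 3 years; iohexol CV 5.5% to 11.6% (Measuring GFR) and about 10% (Sample size calculations, part 3).

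**Assumptions, not in the article.** Two-sided 5% test; unbiased normal errors; a share *f* of each equation's error variance that varies from visit to visit; between-equation error correlation; distribution of GFR and of decline. The closed-form steps use GFR 45 and equation errors that are independent apart from shared iohexol noise.

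**1. Reproduce the article's P30 power.** McNemar power = Φ[(d√n − 1.96√ψ)/√(ψ − d²)], where d is the difference in proportions and ψ the discordant proportion. With d = 0.05, n = 1000 and independence, ψ = 0.81×0.14 + 0.86×0.19 = 0.2768, and power is 85.3%. With ψ = 0.263 it is 87.0%. The stated 87% is reproduced within 2 points.

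**2. Ceiling on the loss.** No test exceeds 100% power. If McNemar's test has over 90% and over 80%, the loss is below 10 and below 20 points. Starting from exactly 90% or 80%, doubling efficiency gives Φ(3.24×√2 − 1.96) = 99.6% and Φ(2.80×√2 − 1.96) = 97.7%, a gain of 9.6 and 17.7 points.

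**3. Closed form, 3 mL cut, f = 0.5, no iohexol error.**
- Proportional error SDs: 0.30/1.311 = 0.229 and 0.30/1.476 = 0.203.
- The squared time deviations sum to 0.25×28 = 7, so slope-error SD = 45×SD×√0.5/√7 = 2.753 and 2.445.
- McNemar: P(|error| > 3) = 27.6% and 22.0%; ψ = 0.374; power 83%.
- Paired test of |error|: mean difference = √(2/π)×(2.753 − 2.445) = 0.246; SE = √[(1 − 2/π)(2.753² + 2.445²)/1000] = 0.0702; ratio 3.50; power Φ(3.50 − 1.96) = 94%.

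**4. The same with iohexol CV 10%.**
- SD of the annualised iohexol change = 45×0.10×√2/3 = 2.12.
- To hold P30 fixed, 0.10² is taken out of each equation's proportional variance. The equations' own parts become 2.476 and 2.129.
- Total SDs are √(2.476² + 2.121²) = 3.261 and √(2.129² + 2.121²) = 3.005. Shared noise gives correlation ρ = 2.121²/(3.261×3.005) = 0.459.
- McNemar: 35.8% v 31.8%, ψ = 0.395, power 51%.
- Paired: mean difference 0.204. The covariance of the two absolute errors, (2/π)σ₁σ₂[ρ arcsin ρ + √(1 − ρ²) − 1], is subtracted twice from the variance sum, so SE = 0.0762; ratio 2.68; power 76%.
- At CV 5.5% the same steps give 71% v 88%.

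**5. Simulation** (n = 1000; P30 81% v 86%; f = 25% or 50%; between-equation correlation 0, 0.3 or 0.6). Power, McNemar v paired |slope error|:

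| Iohexol CV | 3 mL cut | 5% cut | Gain (points) |
|---|---|---|---|
| 0 | 83–92% v 94–99% | 80–95% v 92–99% | 4–14 |
| 5.5% | 66–87% v 84–98% | 60–85% v 82–98% | 11–22 |
| 10% | 39–75% v 61–98% | 29–63% v 55–96% | 22–37 |

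A second simulation over 12 scenarios gave gains of 6–26, 12–26 and 22–38 points in the same three rows. The paired test rejected in about 4% to 5% of null runs. McNemar's test had the lower power in every scenario.

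**6. Runs that meet the stated slope power.** The evaluable number with 15–20% drop-out is 1300×0.80 = 1040 to 1300×0.85 = 1105. In the grid run, both stated powers were reached only with iohexol CV 0–2% and correlation 0.5–0.6, mostly at n = 1105. The gain there was 5–8 points (3 mL) and 9–18 points (5%). One example (n = 1105, f = 0.5, CV 0, correlation 0.6): 94.0% v 99.8%, and 81.5% v 99.5%.

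**The case against.** The strongest reply is that the article powers the study on exactly these binary outcomes, so on its own figures the loss is limited and a real difference would usually be found. That stands as a ceiling, and it is why no single loss can be quoted as the plan's actual loss.

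Second, the large-error rate answers a different question: how often an equation would seriously mislead. It parallels P30, is easy to read clinically and allows comparison with the earlier study. Mean absolute error also counts small errors of little consequence. This stands, and it is a reason to keep McNemar's test.

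Third, full-scale analysis is not wholly absent. The list of study components speaks of accuracy and precision of change in GFR, and the abstract speaks of bias, precision and accuracy. The sub-study of disease progression models error continuously over time. But the general statements name no measure or test for slope error, and the sub-study covers 375 people with no stated test between equations.

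Fourth, a separate analysis plan may add such summaries. That is possible. Here, though, the article itself fixes the test for question 2 and bases power on it, while giving question 1 the continuous summaries.

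**Conclusion.** The point holds as a choice that can be improved. For one of three main questions, the only named between-equation test in the main cohort uses a dichotomised error, with no full-scale counterpart. Some power is lost in every scenario examined. The size is conditional: below 10 points (3 mL cut) and below 20 points (5% cut) if the stated power is right; roughly 11 to 38 points with iohexol CV of 5.5% to 10%. The second range rests on the assumed variance split, correlation, GFR distribution and decline. It is not a bound: a wider grid, with visit-to-visit shares from 10% to 100% and CV 5–10%, reached 41 points (3 mL) and 58 points (5%).

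Three stronger readings are not supported:
- A reader might infer that the stated slope power is wrong, since it was reached here only with almost no iohexol error. The article says that its simulation included random variability but does not give the variance components or the correlation, so its figures can be neither reproduced nor refuted.
- A reader might take change in GFR as the study's central question. It is one of three, and the sample size focuses on P30.
- A reader might conclude that McNemar's test should be replaced. The cuts have a clinical meaning of their own, so the case is for addition.

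No figure is offered for the ethnic, diabetes or proteinuria subgroups.

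**What to change.** In Data analysis, question 2, keep both large-error rates with McNemar's test. Add a pre-specified paired comparison between equations of |eGFR slope − annualised iohexol change|, in mL/min/1.73 m²/year and in %/year, reported as the mean paired difference with a 95% confidence interval (paired t or bootstrap). Add the mean, SD and RMSE of the signed slope differences for each equation, to match question 1.

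The cost is analysis wording and a few lines of code, with no further participants, visits or assays. The downside is one more pre-specified comparison, on a scale that is less directly comparable with the earlier study's large-error percentages. Those percentages are still reported.

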### Progression of kidney disease

There is no consistent definition of what constitutes renal progression in the literature. Many studies have used a doubling of serum creatinine, corresponding to an approximate halving of GFR, as an end-point defining progression, but this is insufficiently sensitive to be useful in clinical practice. Kidney Disease Improving Global Outcomes (KDIGO) have defined progression as a move to a higher disease category (e.g. stage 3A [GFR 45–59 mL/min/1.73 m^2^] to stage 3B [GFR30-44 mL/min/1.73 m^2^]) confirmed by a fall in GFR of greater than or equal to 25%, an increase in albuminuria, a greater than 25% decline in GFR (e.g. a decline from 60 mL/min/1.73 m^2^ to less than 45 mL/min/1.73 m^2^) or a greater than 10%/year decline in GFR (e.g. a decline from 60 mL/min/1.73 m^2^ to less than 54 mL/min/1.73 m^2^ in one year) [38]. NICE defined progression as a decline in GFR of more than 5 mL/min/1.73 m^2^/year, or more than 10 mL/min/1.73 m^2^ averaged over 5 years [6].

Progression is not necessarily common even amongst people with known CKD e.g. amongst people with stage 3 CKD only 1.3% progressed to stage 5 CKD (established renal failure, typically requiring dialysis or transplantation) over 5 years [39]. Amongst community dwelling older (greater than 65 years) adults with stage 3 CKD mean GFR declines of 3.6 mL/min/1.73 m^2^/year and 2.8 mL/min/1.73 m^2^/year have been reported respectively in male and female subjects with diabetes and somewhat lower values amongst subjects without diabetes (1.9 mL/min/1.73 m^2^/year and 1.1 mL/min/1.73 m^2^/year amongst males and females respectively) [40]. In the REIN study proteinuric (greater than 1 g/24 h) non-diabetic subjects with GFRs in the approximate range 30–50 mL/min/1.73 m^2^ showed a decline of GFR of 7.0 mL/min/1.73 m^2^/year with slightly lower values being observed in those receiving renin-angiotensin-aldosterone system (RAAS) blockade [41].

There are some data, mainly restricted to small studies in people with diabetes, describing disease progression in terms of decline in reference GFR measurements [42,43]. Generally, disease progression in people with diabetes has been described as following a broadly linear decline, being influenced by blood pressure and albuminuria and ameliorated by antihypertensive medication/RAAS blockade [42,44,45]. A similar pattern has been observed using estimated rather than measured GFR [46].

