3) Study of intra-individual biological variation

The biological variation of GFR has been estimated at approximately 10% (see above). On this assumption, the sample size (n = 20) and number of repeat samplings proposed will enable the CV_I_ to be estimated within ±2% of its true value.

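### Question 3 defines GFR progression only by an absolute cut worded as KDIGO's, and the apparent prognostic effect of baseline eGFR depends on the scale of that cut

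*Protocol article*

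**What the plan says.** Under Data analysis, Prospective longitudinal cohort study, question 3, the article plans: "Models will be constructed to predict time to progression based on baseline eGFRs and ACR". It wants to know whether the prognostic value of ACR and the eGFRs is independent of other risk factors. Progression is a decline in reference GFR ("change in iohexol GFR > 10 mL/min/1.73 m^2^) or an increase in albuminuria category, as suggested by KDIGO [38"]).

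The Background section Progression of kidney disease sets out KDIGO's definition. KDIGO "have defined progression as a move to a higher disease category", confirmed by a fall of at least 25%; the other criteria are "an increase in albuminuria, a greater than 25% decline in GFR" "or a greater than 10%/year decline in GFR". None is in mL/min. The only 10 mL/min criterion in that section is the one from NICE, "or more than 10 mL/min/1.73 m^2^ averaged over 5 years".

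Question 2 of the same analysis section uses three criteria for change in iohexol GFR: more than 25%, a decline of at least 10 mL/min/1.73 m² over three years, and a change beyond the reference change value (RCV). Question 3 keeps only an absolute one.

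Variation of measured GFR is given as a CV: 5.5% to 11.6% in Measuring GFR and, for planning, "The biological variation of GFR has been estimated at approximately 10" per cent in Sample size calculations.

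**The concern.** There are two linked problems. First, the sentence invites the reader to take the whole definition as KDIGO's, although the GFR part does not match KDIGO as the article reports it.

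Second, the outcome is a fixed number of mL/min and the predictor under test is the baseline level of nearly the same quantity. Ten mL/min is a 33% fall from 30 but a 17% fall from 59. If measurement error is proportional to GFR, or if people lose a similar percentage, those with higher baseline GFR cross the line more often. The sign and size of the baseline eGFR coefficient, and hence any statement about its independent prognostic value, may then reflect the scale of the cut and not the disease.

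**Working it through.** **The protocol's own figure.** No error rate is stated for the 10 mL/min rule. The nearest figure is the RCV of 14.4% for MDRD eGFR in Identifying progressive kidney disease. With CV_I 5.4% and CV_A 3.0%, 1.645 × √2 × √(5.4² + 3.0²) = 14.4%, so it reproduces with a one-sided z. The article itself thus judges real change on a relative scale.

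**Step 1: noise alone, no true change.** For two iohexol measurements at true GFR *G*, the difference has SD *G* × CV × √2.
- P(fall > 10) = 1 − Φ(10 / (*G* × CV × √2)). At CV 10% and *G* = 59: SD 8.34, z = 1.20, P = 11.5%. At *G* = 30: SD 4.24, z = 2.36, P = 0.9%.
- P(fall > 25%) = Φ(−0.25 / (CV × √(1 + 0.75²))), which does not contain *G*. At CV 10%: z = −2.0, P = 2.3%.

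| CV | >10 mL/min, at 30 / 45 / 59 | >25%, any baseline |
|---|---|---|
| 5.5% | 0.0% / 0.2% / 1.5% | 0.01% |
| 10% | 0.9% / 5.8% / 11.5% | 2.3% |
| 11.6% | 2.1% / 8.8% / 15.1% | 4.2% |

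**Step 2: add only the ageing decline the article cites**, about 1 mL/min a year, so 3 over the study, with CV 10%. At baseline 30 / 45 / 59 the 10 mL/min rule gives 4.1% / 12.8% / 19.5%, and the 25% rule gives 10.0% / 6.3% / 5.0%. The two gradients run in opposite directions.

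**Step 3: association with baseline.** Simulation of 300,000 people. Assumptions: baseline GFR uniform on 30 to 59, iohexol CV 10%, eGFR log-error SD 0.20. Constant-percentage decline has mean 4.5% and SD 4.5% per year; constant absolute decline has mean 2 and SD 2.5 mL/min per year. The GFR limb only is modelled. Odds ratios are per 10 mL/min.

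| True course | >10 cut: true GFR / eGFR | >25% cut: true GFR / eGFR |
|---|---|---|
| No change | 2.1 / 1.3 | 1.00 / about 1.0 |
| Constant percentage | 1.67 / 1.25 | 1.00 / 1.00 |
| Constant mL/min | about 1.06 / 1.03 | 0.67 / 0.83 |

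Question 3 tests eGFR, so the eGFR figures are the relevant ones.

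**Step 4: how much is noise?** In the constant-percentage scenario the >10 cut gives 2.2 on true GFR with no measurement error and 1.67 with CV 10%. Noise weakens that association; it does not create it.

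**Step 5: ranking the equations.** With no true change, CV 10%, true GFR uniform on 30 to 60 and unbiased eGFRs, the AUC for false progression by the 10 mL/min rule is 0.609 for an equation with P30 81% and 0.616 for one with P30 86%. Under the 25% rule both are about 0.50.

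**The case against.** **The attribution may be correct.** The KDIGO clause follows the albuminuria limb, and the Background does list an increase in albuminuria under KDIGO. This stands: the sentence is ambiguous and not demonstrably wrong. Even on that reading, though, the GFR limb has no stated source.

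**An absolute cut is a legitimate estimand.** NICE's criteria, the decline rates cited in the Background and the planned progression model are all in mL/min/1.73 m². This also stands. What does not follow is that one absolute cut is enough when baseline level is the predictor and question 2 already uses three definitions.

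**The 25% cut carries its own baseline dependence.** This stands too. The Background describes decline in diabetes as broadly linear, and the analysis of the progression sub-study leaves linear or exponential decline open. The documents therefore do not establish the pattern under which a 25% cut would be neutral.

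**Sensitivity definitions may be in the full protocol or SAP.** Possibly, and their absence from an article is not the point. The point is the single definition that the article does fix, and how it is worded.

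**Conclusion.** The point holds in limited form. The GFR limb of question 3 rests on one scale-dependent cut whose wording suggests a KDIGO origin that the Background does not support. The baseline eGFR odds ratio per 10 mL/min moves between about 1.25 and 1.00 (constant-percentage decline) or between 1.03 and 0.83 (constant absolute decline) merely by switching from the 10 mL/min to the 25% cut.

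Three stronger conclusions might be inferred, and none is supported:
- *That measurement noise alone drives the association.* This is so only when nobody truly declines, whereas the cohort is enriched for progression. Under constant-percentage decline the association follows from choosing an absolute outcome.
- *That the 25% cut is the unbiased choice.* It is neutral under no change or constant-percentage decline only.
- *That the comparison between equations is distorted.* All equations face the same outcome, and the AUC difference is 0.007.

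The noise-only figures assume error proportional to GFR, which the article's use of CVs supports; constant absolute error would remove that gradient. They are material at the planning CV of 10% and involve few people at 5.5%. The albuminuria limb is not modelled and would dilute all of these effects.

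**What to change.** 1. State which part of the definition comes from KDIGO, and give the source or rationale for the 10 mL/min/1.73 m² limb.
2. Fit the question 3 models with the >25% and RCV definitions of question 2 alongside >10 mL/min.
3. State in advance that baseline eGFR will be said to have independent prognostic value only if the result is consistent across the definitions.

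Replacing the absolute cut by 25% as the sole main definition is not recommended, because it exchanges one baseline dependence for another.

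The cost is a short wording change and a few more model fits; the definitions are already derived for question 2. The 25% cut yields somewhat fewer events: about 23% against 29% in the constant-percentage scenario.

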**Figure 1 F1:**
[figure not shown]
General study schema.

There are five components to the study:

1) A 3-year prospective longitudinal cohort study using 6-monthly estimates of GFR and baseline and final reference GFR values to assess and compare the accuracy and precision of each estimate of GFR and change in GFR. This will include assessments in high risk subgroups and ethnic groups.

2) Investigation and modelling of patterns of progression of GFR in a subset of the cohort, stratified by ethnicity, presence of diabetes and proteinuria, who will receive annual reference GFR, assessing risk factors and over time.

3) A sub-study investigating sources of variability to estimate the components of measurement error in each measure and estimate of GFR.

4) Using information from 1), 2) and 3) modelling of alternative monitoring strategies, using different estimates of eGFR and monitoring frequencies.

5) A model-based cost-effectiveness analysis.

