### Prospective longitudinal cohort study

The primary study will comprise a prospective longitudinal cohort study in which adults (n = 1300) with stage 3 CKD, enriched to include people more likely to have progressive kidney disease (i.e. those with proteinuria and/or diabetes), will be recruited from six UK centres. Participants will be recruited from both primary (two centres) and secondary/tertiary (four centres) care. People aged 18 years and older having stage 3 CKD (eGFR measurements between 30 and 59 mL/min/1.73 m^2^ inclusive sustained over at least 3 months prior to recruitment) will be included. Recruitment will be targeted such that 20% to 30% of recruits will have proteinuria (ACR ≥30 mg/mmol) and a similar proportion will have diabetes. The prevalence of proteinuria and diabetes will be monitored during the course of the study to ensure reasonable representation.

Participants will attend hospital in the morning having been advised to consume a light breakfast (no meat or fish). A clinical (including cardiovascular) and drug history will be recorded using a standardised questionnaire. Information on ethnicity will be gathered using a modified version of the 2011 UK Census Questionnaire. Height will be measured to the nearest 0.1 cm with a rigid stadiometer. Body weight will be measured in light indoor clothing to the nearest 0.1 kg. Waist circumference will be recorded to the nearest 0.1 cm at the mid-point between the lower costal margin and the level of the anterior superior iliac crest. Hip circumference will be measured at the widest point of the hips and the maximal protrusion of the gluteal muscles. Brachial blood pressure will be measured three times in the sitting position as recommended [56]. Blood will be taken for serum creatinine, cystatin C and a urine sample will be collected for ACR. Further aliquots of serum, plasma and urine will be stored for potential analysis of future markers of GFR. An iohexol reference GFR measurement will be undertaken in addition to estimation of GFR using four GFR estimating equations (MDRD, CKD-EPI_creatinine_, CKD-EPI_cystatin_, and CKD-EPI_cystatin-creatinine_) (Table 1).

Participants will be followed for three years. All the above measurements and the clinical questionnaire will be repeated at 36 months. At each 6 month interval, all participants will have blood taken for serum creatinine, cystatin C and a urine sample will be collected for ACR. GFR will be estimated as above.

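### Question 3 assumes progression can be detected at six time points, but iohexol GFR has one post-baseline measurement in most participants and six in none

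*Protocol article*

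**What the plan says.** In the protocol article, *Data analysis*, *Prospective longitudinal cohort study*, question 3, the outcome is a time: "Models will be constructed to predict time to progression based on baseline eGFRs and ACR". The event is an either-or composite, "decline in reference GFR (change in iohexol GFR > 10 mL/min/1.73 m^2^) or an increase in albuminuria category". The choice of model follows from a statement about when events can be seen: "Progression will only be detected at one of 6 time points, hence piecewise survival models will be fitted".

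The measurement schedule is given elsewhere:

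- **Reference GFR, whole cohort.** *Methods/design* describes the cohort component as a "3-year prospective longitudinal cohort study using 6-monthly estimates of GFR and baseline and final reference GFR values". The cohort section lists iohexol among the baseline procedures and adds: "All the above measurements and the clinical questionnaire will be repeated at 36 months".
- **Reference GFR, sub-study of 375.** The abstract states: "Additional reference GFR measurements will be undertaken after 1 and 2 years".
- **Creatinine, cystatin C and ACR, everyone.** The abstract states: "Test measurements will also be undertaken every 6 months".

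**The concern.** A piecewise survival model on a common visit grid assumes that an event occurring in an interval can be seen at the end of that interval. Here the two components of the event are observed on different grids, and the GFR grid also differs between participants.

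Three consequences follow for participants outside the sub-study:

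1. Intervals 1 to 5 can contain only albuminuria events. The GFR hazard is zero there by construction and falls entirely in interval 6. Any non-proportional effects found would partly describe the visit calendar.
2. In a first-event analysis, someone whose albuminuria category rises early leaves the risk set before a GFR fall can be observed.
3. Baseline ACR, a predictor, is set against a composite with six looks for later ACR and one look for GFR. That matters because question 3 asks whether ACR alone, or an eGFR with ACR, predicts best.

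A further problem is conditional. If the sub-study's 12- and 24-month iohexol values count as events, the extra looks are tied to ethnicity, which is a covariate in the same model.

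**Working it through.** **1. The plan's figure of six.** Follow-up is 36 months with visits every 6 months: 36 / 6 = 6 post-baseline visits, or 7 with baseline, which matches the maximum of 7 eGFR time points under question 2. The figure reproduces for ACR and eGFR.

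**2. Detection times by component.**

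| Component | Participants | Post-baseline times |
|---|---|---|
| Albuminuria category | all 1300 | 6 (months 6 to 36) |
| Iohexol GFR, outside sub-study | 1300 − 375 = 925 (71.2%) | 1 (month 36) |
| Iohexol GFR, sub-study | 375 (28.8%) | 3 (months 12, 24, 36) |

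With the 15–20% drop-out in *Sample size calculations*, 1300 × 0.85 = 1105 or 1300 × 0.80 = 1040 complete. If the sub-study is fully retained, (1105 − 375)/1105 = 66% or (1040 − 375)/1040 = 64% of completers still have a single GFR detection time.

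**3. Timing, by simulation.** Assumed: linear decline, mean slope −1.5 to −3.6 mL/min/1.73 m²/year, between-person SD 2 to 3, no measurement noise. True falls beyond 10 within three years then occur on average at 22.6 to 28.2 months, and 22–60% of them by month 24. Outside the sub-study all are recorded at month 36.

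**4. Effect of extra looks, only if interim iohexol values count.** Assumed: baseline GFR uniform 30–60, slope mean −2 and SD 2, the same in both groups. The CVs lie within the 5.5–11.6% range quoted under *Measuring GFR*.

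| CV | Fall >10 at month 36 | Fall >10 at month 12, 24 or 36 | Odds ratio, identical biology |
|---|---|---|---|
| 5.5% | 28% | 30% | 1.07 |
| 10% | 32% | 39% | 1.36 |
| 11.6% | 34% | 43% | 1.46 |

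Odds ratios use unrounded shares. On the sub-study schedule, 44% (CV 5.5%) to 67% (CV 11.6%) of GFR events would be recorded before month 36, against none on the main schedule.

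**5. Dilution to an ethnicity effect.** The sub-study has 250 of 375 participants (two thirds) of African-Caribbean or Asian origin. The article gives no cohort totals by ethnicity. Its stated 95% intervals for P30, 10 points wide, imply n = 1.96² × p(1 − p)/0.05², which is 236 at p = 0.81 and 185 at p = 0.86. Then 125/236 = 53% to 125/185 = 68% of each minority group would have interim iohexol. Among the remaining participants, taken as Caucasian, the share is 125/(1300 − 370) = 13% to 125/(1300 − 472) = 15%. With no true ethnic difference, mixing the event shares in these proportions gives a spurious odds ratio for any GFR event of about 1.03–1.04 at CV 5.5% and 1.12–1.18 at CV 10%. This covers event proportion only, not timing.

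**The case against.** The strongest reply is that the sentence is literally true of the composite. Every visit that can show either component lies on the same six-point grid, and the article does not claim six iohexol measurements. Albuminuria events are also observed every six months, so their timing is real to within a visit interval. Both points stand. They do not rescue the model, because one grid for the composite still treats intervals 1 to 5 as if a GFR event could have been seen in them.

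A reader might go further and infer that the analysis is biased for ethnicity, diabetes and ACR because sub-study participants get extra looks. The document does not establish this:

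- Question 3 never says that the interim iohexol values count. *Methods/design* describes the cohort component by its baseline and final reference values, and the annual values are assigned to a separate random-coefficients model. On that reading everyone has one GFR look and the differential bias disappears.
- Over-representation of high-risk people in the sub-study is not shown. About half have diabetes and/or proteinuria, but the whole cohort is enriched to 20–30% for each. If these are independent, 1 − 0.8² = 36% to 1 − 0.7² = 51% have at least one.
- At CV 5.5% the excess in event share is small, and no shift in the ranking of equations has been demonstrated.

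It can also be said that a piecewise hazard may be fitted with an interval-censored likelihood, and that such detail belongs in an analysis plan. That is fair for the likelihood. But the article itself fixes the endpoint, the number of detection times and the model class, and the premise linking them does not fit the GFR schedule.

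**Conclusion.** The point holds for the GFR component and for the composite time built from it. It does not hold for albuminuria event times. The core rests on counting visits and needs no simulation: one post-baseline iohexol measurement in about 71% of participants, three in about 29%, six in none. Followed as written, question 3 would yield early intervals made up of albuminuria events alone for most participants, and GFR event times set by the calendar.

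Distortion of the ethnicity effect is conditional on counting interim iohexol values. Its size depends on assumed slopes, CV and group totals, and ranges from slight at CV 5.5% to moderate at CV 10%. Bias in the diabetes and ACR effects is possible but not shown. It would be too strong to say that event times in general reflect the test schedule rather than the disease. The P30 comparison and its sample size are unaffected.

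**What to change.** Analyse the two components on their own schedules:

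- **Iohexol progression:** a binary outcome at 36 months, using baseline and 36-month values only, for everyone. Question 2 already uses a three-year GFR decline as a yes/no target.
- **Albuminuria progression:** a separate discrete-time model over the six ACR visits.

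If a time-to-event model is kept for GFR, use an interval-censored likelihood with each participant's actual iohexol measurement times. State explicitly whether the 12- and 24-month sub-study values count.

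The cost is wording only, with no new data. The analysis would give no within-study GFR event time for the main cohort, but two measurements per person cannot supply one anyway. Whether to add established renal failure before month 36 as an event is a separate outcome decision and not part of this correction.
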